### *7.13.3 Completed Cases Population*

---

The Completed Cases (CC) population is defined as all enrolled subjects and eligible patients who received at least one dose of study-directed treatment (medication) and had 180 days of follow-up defined as any efficacy measurement taken at this visit.

### *7.13.4 Per-protocol Population*

---

The Per-protocol population (PP) population is a subset of CC population and it includes all enrolled patients entirely consistent with the Protocol and who received at least 80% of study-directed treatment and had 180 days of follow-up. Any visits where Protocol violations occurred will be reviewed for possible exclusion from PP population.

The patients with major Protocol violations will be tabulated by violation type and affected visit(s), where applicable. All Protocol violations will be listed.

### *7.13.5 Primary Analysis Populations*

---

Primary efficacy analysis will be performed on the ITT population. Primary safety analysis will be performed on the mITT population.

## *7.14 Randomization*

---

The randomization will be performed at 1:1 ratio between the investigational and control arms. Randomization will be carried out according to the blocks procedure. Block randomization is used to assign eligible subjects to the treatment arms in order to avoid serious imbalance in the number of subjects assigned to each group within a center. The pattern of the blocks will be concealed to avoid selection bias. Two block sizes will be used, with 2 and 4 subjects per block. Block sizes will be chosen at random. This scheme makes breaking the blinding by working out the block pattern extremely difficult and reasonably protects against biased allocation of subjects.

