|-------------------------------------|----------------------------------------------------------------------------------------------------------------------------------------------------------------------------------------------------------------------------------------------------------------------------------------------------------------------------------------------------------------------------------------------------------------------------------------------------------------------------------------------------------------------------------|--------------------------------|
| Phase                        | II/III                                                                                                                                                                                                                                                                                                                                                                                                                                                                                                                           |                                |
| Study Type                   | Interventional                                                                                                                                                                                                                                                                                                                                                                                                                                                                                                                   |                                |
| Study Design                 | Allocation:                                                                                                                                                                                                                                                                                                                                                                                                                                                                                                                      | Randomized, stratified by site |

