### *6.7.4 Blinding*

---

Subjects, Investigators, and study research personnel will be blinded to the subject treatment arm allocation. The AOSpine North America Methods Core will maintain link between the randomization information and the Investigational Drug information. This information will be accessible only to selected restricted personnel at the Methods Core, which will not include study monitors or other personnel in direct contact with the study sites. Treatment allocation will be un-blinded for the purpose of interim analysis presented to the DSMB. The results of the interim analysis and the un-blinded data will not be shared with Investigators, subjects or those involved in the execution of the study. Emergency un-blinding for the safety reasons will be permitted. Sites will be supplied with emergency un-blinding materials.

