### *6.7.5 Enrollment*

---

Subject enrollment occurs at the time of Randomization. If a subject is consented, screened and for any reason does not get randomized, the subject will NOT be considered enrolled in the study.

The randomization will occur by opening the lowest sequential number of the sealed randomization envelopes at each specific site. Inside the envelope there will be a unique subject randomization number. The authorized research staff will match the unique subject

randomization number with the number on the Investigational Drug container. The randomization will be recorded in the Randomization Log.

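### Section 7.14 prints block sizes 2 and 4 in a protocol that sites hold, so its assurance that the block pattern is very hard to work out is too strong once one allocation is known

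*Protocol*

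**What the plan says.** Section 7.14 (Randomization) sets the ratio: "The randomization will be performed at 1:1 ratio between the investigational and control arms". It relies on concealment: "The pattern of the blocks will be concealed to avoid selection bias". The next sentences describe the scheme: "Two block sizes will be used, with 2 and 4 subjects per block" and "Block sizes will be chosen at random". The section then concludes: "This scheme makes breaking the blinding by working out the block pattern extremely difficult and reasonably protects against biased allocation of subjects".

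Other sections decide what a site can see:

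- The Synopsis describes allocation as "Randomized, stratified by site", so each site runs its own block sequence.
- Section 6.7.5: "The randomization will occur by opening the lowest sequential number of the sealed randomization envelopes at each specific site". Each randomization is entered in a log, so the order is visible to site staff.
- Section 6.7.4: "Sites will be supplied with emergency un-blinding materials". Under section 6.7.7.13 the site's principal investigator decides whether to use them.
- Section 10.3 has each investigator sign the protocol, and section 10.6 has the site keep all versions. Nothing says that section 7.14 is withheld from sites.

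**The concern.** Randomly varying block sizes protect allocation only as far as the site cannot place the block boundaries. Here the site is told both sizes, sees the order of its subjects and can learn an individual allocation through a code break. With sizes 2 and 4 only, random choice between them hides little, because every block ends at an even position.

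A code break is meant to reveal one subject's arm. If it also makes a neighbour's arm guessable well above chance, two things are exposed. If the unblinded subject has an odd number in the site's sequence, the pair partner is the next subject, and the decision to enrol could be influenced. If the number is even, the partner is already in the trial, and later ratings could be influenced. The primary endpoint is the change in ISNCSCI motor score to 180 days (section 6.3.1), which is scored by an examiner (section 6.7.7.9), so masking of the rater matters.

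**Working it through.** The protocol gives no predictability figure to reproduce, so the check works from the stated scheme.

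**Inputs.** Ratio 1:1, block sizes 2 and 4, chosen at random (section 7.14). Separate sequences by site (Synopsis). Up to 35 sites and 351 subjects (section 6.1), so about 351/35 = 10 subjects per site. The weights of the two sizes are not stated. Equal weights are assumed, and a range of 25:75 to 75:25 is shown.

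**Pairs.** Every block has even length, so every block starts at an odd position. Subjects 1-2, 3-4, 5-6 and so on are therefore always in the same block. Two subjects in a block of 2 are opposite with probability 1. Two subjects in a block of 4 are opposite with probability 2/3.

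**First pair.** P(subject 2 opposite to subject 1) = 0.5 × 1 + 0.5 × 2/3 = 0.833.

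**Later pairs.** Let r(k) be the probability that a new block starts at pair k. Under equal weights r(1) = 1, r(2) = 1/2, and r(k) = [r(k-1) + r(k-2)]/2. This gives 3/4, 5/8 and 11/16 for pairs 3 to 5, with long-run value 2/3. Pair k is a whole block of 2 with probability r(k)/2, so

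P(partner opposite) = 2/3 + r(k)/6.

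Across the boundary between pair k-1 and pair k, the two subjects share a block of 4 with probability 1 - r(k) and are otherwise independent, so

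P(neighbour opposite) = (2/3)(1 - r(k)) + (1/2) r(k) = 2/3 - r(k)/6.

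| Pair k | r(k) | Partner within pair opposite | Across boundary from pair k-1 |
|---|---|---|---|
| 1 | 1 | 0.833 | n/a |
| 2 | 0.500 | 0.750 | 0.583 |
| 3 | 0.750 | 0.792 | 0.542 |
| 4 | 0.625 | 0.771 | 0.562 |
| 5 | 0.688 | 0.781 | 0.552 |
| Long run | 0.667 | 0.778 (7/9) | 0.556 (5/9) |

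Exact enumeration of all sequences of 10 subjects gives the same values.

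**Unequal weights.** If size 2 has weight w, the partner probability is 2/3 + w r(k)/3. Over w from 0.25 to 0.75 and pairs 1 to 5, the lowest value is 2/3 + 0.25 × 0.25/3 = 0.69 (pair 2, w = 0.25). The highest is 2/3 + 0.75/3 = 0.92 (pair 1, w = 0.75).

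**Comparison with a fixed block of 4.** Averaged over the nine adjacent steps among 10 subjects, the next subject is opposite with probability 0.69, against 0.63 for a fixed block of 4 with the same single allocation known. Mixing in blocks of 2 therefore raises predictability after one code break.

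**Two known allocations.** Subjects 1 and 2 share an arm with probability 0.5 × 1/3 = 1/6, or 17%. They must then be in a block of 4, and subjects 3 and 4 are both in the other arm with certainty.

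**Larger sizes, for illustration.** With sizes 4 and 6, equally weighted, the first-pair figure is 0.5 × 2/3 + 0.5 × 3/5 = 0.63. If subjects 1 and 2 are known to be equal, subjects 3 and 4 are both opposite with probability (1/6 + 1/5 × 1/2)/(1/6 + 1/5) = 0.73 rather than 1.

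**The case against.** Most of the opposing case stands, and it limits the point.

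- **Not a contradiction.** A reader might infer that section 7.14 contradicts itself by concealing the pattern and then printing it. It does not. It discloses two possible sizes, while the order of sizes and the permutations stay hidden.
- **The probabilities come from small blocks, not from disclosure.** Anyone who knows that permuted blocks are used would guess the opposite arm after a code break, and at position 2 would be right with probability 0.83 whether or not the sizes are printed. Printing them adds the odd-even pair boundaries and the certainty after an equal pair.
- **The trigger is restricted.** Section 6.7.7.13 limits code breaks to cases where care and safety require them, with documentation and a report within 24 hours. Under section 6.7.2.3, meeting the liver criteria does not in itself break the blind. Placebo capsules match except for the active content (section 5.2.8.1), and containers look identical (section 6.7.7.12). The protocol gives no expected number of code breaks.
- **Liver enzymes are a weak clue.** A reader might infer that enzyme results unmask subjects. Table 6 (ALS trials) gives abnormal ALT in 29% v 14% and AST in 23% v 19%. At 1:1, an abnormal ALT implies riluzole with probability 29/43 = 0.67, and an abnormal AST 23/42 = 0.55. Taking the ALT figure through to the first-pair partner gives 0.67 × 0.83 + 0.33 × 0.17 = 0.62. Section 5.2.6.2 also reports raised AST on admission in 37% of SCI patients. These rates may not transfer to 14-day dosing, but the protocol offers no stronger evidence.
- **Enroller and rater may differ.** A reader might infer that the same person enrols and later rates a subject. Section 6.7.7.9 assigns the 180-day examination to the investigator, section 6.7.5 has research staff handle randomization, and section 6.7.7 allows an assigned examiner for visits outside the clinic. Overlap is neither excluded nor established.

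What remains is that the assurance in section 7.14 is not supported for sites that hold this text, their own sequence and the code breaks.

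**Conclusion.** The point holds as a modest one. After one code break, the pair partner's arm can be guessed correctly with probability 0.83 for a site's first pair and 0.75-0.79 for later pairs, against 0.50 by chance. The full range is 0.69-0.92 for size weights between 25:75 and 75:25. The neighbour on the other side is close to chance, at 0.54-0.58. Certainty about a later subject needs two known allocations that happen to be equal, which for subjects 1 and 2 occurs in 17% of sequences. It would therefore be wrong to say that one code break determines the neighbouring allocations.

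The figures assume equal size weights where no range is given. That sites know the sizes is inferred from their signing and filing the protocol. No bias in the primary analysis is shown, and the sample size and error rates are unaffected. The change is worth making because it is cheap and the primary endpoint is scored by an examiner.

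**What to change.** 1. In section 7.14, state only that permuted blocks of randomly varying size within site are used. Remove the sizes.
2. Keep the sizes and their weights in a randomization document restricted to the Methods Core staff who hold the code under section 6.7.4.
3. Delete or soften the closing assurance about working out the block pattern.
4. Generate envelopes not yet issued with larger, undisclosed sizes. This step is needed because deletion alone leaves the probabilities as they are, and sites already hold the current version. Sizes 4 and 6 are an illustration only: they would lower the first-pair figure from 0.83 to 0.63. The sizes chosen should not appear in any document that sites hold.

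The cost is an amendment to wording, some list generation and slightly looser balance within site. The largest possible imbalance inside a block is half its size, so it would rise from 2 to 3 in the 4-and-6 illustration. Endpoint, analysis and sample size do not change.

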## *7.15 Evaluation of 365 days follow-up data*

---

365 days follow-up will be available for majority, but not for all subjects. The main purpose of the 365 days follow-up data is to evaluate sustainability of the possible effect. The sustainability analysis will be based on repeated measurement analysis and testing of interaction terms between the treatment arm and follow-up time as well as Bayesian analytic approaches. The details will be described in SAP.

### *7.16 Pre-planned Subgroup Analyses*

---

A pre-planned sub-group analysis will be conducted to evaluate differences in  $\Delta$ ISNCSCIMS180-b among the patients in baseline ISNCSCI Impairment Groups “A,” “B” and “C.” The rationale for this pre-planned analysis is that these groups experience different recovery of ISNCSCIMS which may result in between-group differences in  $\Delta$ ISNCSCIMS180-b. Motor recovery, as measured by change in ISNCSCIMS between acute admission and 6 months follow-up, is known to vary according to individuals’ baseline level of injury severity, as defined by ISNCSCI grade. For instance, for cervical patients, in data obtained from the NACTN prospective registry, the average improvement in ISNCSCIMS from admission to 6 months follow-up was 12.4 (SD=22.3) points for ISNCSCI grade “A” patients, 27.0 (SD=26.3) points for ISNCSCI grade “B” patients and 52.3 (SD=24.1) points for ISNCSCI grade “C” patients. The variability in motor recovery depending on the baseline injury severity has been fully incorporated into the sample size estimate calculations described in Section 7.9. At present, the data from the Phase I study of riluzole in SCI are under analysis. Such data, when available, will be incorporated in the planning of this sub-group analysis. However, this pre-planned sub-group analysis is of interest from an exploratory perspective and will be used for purposes of planning future studies which may serve to further refine riluzole’s role in the treatment of SCI. Statistical details of this analysis will be provided in the SAP.

Other pre-planned sub-group analyses may be performed. They will be pre-specified in the SAP before any study data is un-blinded or analyzed for efficacy.

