| Statistical Plan      | 
The statistical analysis will test the null hypothesis of the superiority of riluzole compared to placebo in change of ISNCSCI Motor Score between the baseline and the 180-day follow-up (<math>\Delta</math> ISNCSCIMS).
 
Statistical Test. The statistical testing of <math>H_0</math> for the primary endpoint will be organized as a 2-stage sequential adaptive design. There will be one interim analysis at about 60% of the accrued sample and the final analysis. The overall sequential design will be organized in the following way. The statistical design will address efficacy and futility. The statistical testing of <math>H_0</math> hypothesis will be performed as a one-way test with alpha level .025, testing the superiority of riluzole arm compared to placebo arm. The superiority of placebo over riluzole (i.e. harmful effect of riluzole) will not be tested as it has no clinical implication. Alpha-spending for the testing of <math>H_0</math> will resemble an O'Brien-Fleming distribution. The testing for futility (<math>H_1</math>) will consequently be organized as one-way testing. The beta spending for futility testing will follow <math>\gamma</math>-distribution with the parameter (-1). The results of the interim analysis will be reviewed by the DSMB and will not be shared with the sponsor, participating investigators or patients, except in the case that the study reaches stopping criteria.
 
Sample Size. Based on the above statistical design specifications and empirically-derived standard deviation for ISNCSCIMS change of 24.08 from a large case series of prospectively followed SCI subjects in an earlier study, a sample size of 316 subjects (158 in each arm) will have 90% power to detect 9 points difference in the <math>\Delta</math> ISNCSCI Motor Score at one-sided <math>\alpha = .025</math>. To account for losses to follow-up of up to 10%, the study will enroll 351 subjects.
 
The sample size estimate is based on certain assumptions. The main assumptions affecting the sample size is that of the true effect size and the standard deviation for the difference in the <math>\Delta</math> ISNCSCIMS. These assumptions will be verified during the study and sample size adjustment will be performed if needed, using the adaptive techniques. The sample size adjustment will be performed after the first interim analysis of the data, currently planned at about 60% of the data available at 180 days follow-up. The details of the adaptive design will be provided in a separate Statistical Analysis Plan (SAP).
 
Study success. Study will be considered to successfully confirm the working hypothesis if <math>H_0</math> for the primary endpoint has been rejected either at interim or the final analysis.
 
Secondary outcomes. Testing for all secondary outcomes will be based on appropriate statistical methods and two-way superiority testing. Secondary outcomes will not be tested at the interim analysis, except if
 |

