### 7.6 Statistical Testing of Primary Endpoint

---

The appropriate statistical approach is to test a single one-sided null-hypothesis that the difference between the investigational and the placebo arm is equal to or less than 0. Rejection of the null-hypothesis is consistent with superiority of the investigational treatment to the placebo.

$$H_0: \mu_I - \mu_C \leq 0$$

$$H_1: \mu_I - \mu_C > 0$$

Where:

$\mu_I$  and  $\mu_C$  are the means of the two independent normal distributions;

$\mu_I$  is the mean population value of the  $\Delta$ ISNCSCIMS180-b in the patients treated with riluzole;

$\mu_C$  is the mean population value of the  $\Delta$ ISNCSCIMS180-b in the patients treated with placebo.

The hypothesis will be tested by one-sided t-test at the alpha level of 0.025. If the test value exceeds the nominal critical point, the  $H_0$  will be rejected. If the test-value crosses the futility boundary, the  $H_0$  will be accepted.

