### 7.9 Sample Size Estimate

The required sample size is 316 evaluable subjects, or 158 subjects per study arm. The rationale for the sample size is as follows.

Sample size has been calculated to provide 90% power in testing the primary superiority hypothesis. The estimate has been calculated by PROC SEQDESIGN for SAS/STAT. Standard deviation for the primary outcome parameter has been made using the data from the STASCIS study (data on file with the Sponsor) (Table 3). This estimate is based on subjects with neurological level of injury from C4-C8 at arrival, the ISNCSCI Impairment grade “A,” “B” or “C” and time from injury to arrival of less than 12 hours.

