**Table 4 Sample size estimate  $\Delta$ ISNCSCIMS180-b**

| Plan ID                                           | Parameter            |
|---------------------------------------------------|----------------------|
| Type of the Hypothesis                            | 1-Sided              |
| Type I Error ( $\alpha$ )                         | 0.025                |
| Power (1 - $\beta$ )                              | 0.90                 |
| Randomization Ratio (Investigational vs. Control) | 1:1                  |
| Planned Number of Interim Looks                   | 2                    |
| Spacing of Looks                                  | 60%, 100%            |
| Hypothesis to be Rejected                         | H0 or H1 (binding)   |
| Boundary Family                                   | Published Function   |
| Boundary to Reject H0                             | Est. O'Brien-Fleming |
| Boundary to Reject H1                             | Gamma (-1)           |
| Difference of Means Assuming H 1       | 9                    |
| Standard Deviation ( $\sigma$ )                   | 24.08                |
| Sample Size                                       | 316 (158 per arm)    |

Under the above assumptions, the estimated sample size is 316 evaluable subjects (158 in the riluzole arm and 158 in the placebo arm). In order to account for loss of power due to loss of follow-up and possible adjustments for baseline factors we will increase sample size by 10% to **351 enrolled** subjects.

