### *7.10 Justification for Effect Estimate*

There is no published minimally significant difference for ISNCSCIMS. The current effect estimate of 9 is arbitrarily set. This difference translates to 0.37 Cohen's d and is at the lower boundary of the moderate effect.

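### The 90% power rests on a standard deviation of 24.08 that the protocol does not reconcile with its own grade-specific recovery figures; adjusting the primary test for baseline grade would remove most of the dependence

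*Protocol*

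**What the plan says.** Protocol Section 7.9 and Table 4 plan a two-look group-sequential comparison of mean change in motor score from baseline to 180 days. The inputs are a 9-point difference, SD 24.08, one-sided alpha 0.025 and 90% power: "Under the above assumptions, the estimated sample size is 316 evaluable subjects". Section 7.10 says of the difference: "The current effect estimate of 9 is arbitrarily set".

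Section 7.9 takes the SD from an earlier study, in subjects with C4-C8 injury, grade A, B or C, and arrival within 12 hours. The Synopsis describes it as an "empirically-derived standard deviation for ISNCSCIMS change of 24.08 from a large case series of prospectively followed SCI subjects in an earlier study".

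Section 7.6 fixes the test: "The hypothesis will be tested by one-sided t-test at the alpha level of 0.025". It names no covariate. The Synopsis stratifies randomization by site only, and Section 7.14 describes blocks within centre.

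Section 7.16 gives registry figures for six-month motor change in cervical patients: mean 12.4 (SD 22.3) for grade A, "27.0 (SD=26.3) points for ISNCSCI grade" B, and 52.3 (SD 24.1) for grade C. It then states that the variability in recovery by baseline severity "has been fully incorporated into the sample size estimate calculations described in Section 7.9".

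**The concern.** A t-test without covariates on a mixed A/B/C sample faces the total variance of the change score: the variance within grades plus the variance between grade means. The registry means span about 40 points (52.3 − 12.4 = 39.9), so the second part is large unless one grade dominates. The registry SDs within grade are 22.3, 26.3 and 24.1. A total SD of 24.08 leaves little room for any difference between grades.

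If the enrolled sample behaves like the registry and contains a fair share of grades B and C, the risk of missing a true 9-point effect exceeds the planned 10%. The sentence in Section 7.16 tells the reader that this has been taken care of, but the protocol gives neither a grade mix nor a calculation to support it.

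**Working it through.** **1. Reproduce the plan's own figure.** Inputs from Section 7.9, Table 4 and the Synopsis: difference 9, SD 24.08, one-sided alpha 0.025, power 0.90, 1:1 allocation, looks at 60% and 100%, O'Brien-Fleming-type alpha spending, gamma(−1) beta spending, binding futility.

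Spending at the interim is 0.00381 (alpha) and 0.04785 (beta). Solving the boundaries gives z-values of 2.669 (efficacy) and 0.906 (futility) at the interim, 1.936 at the final look, and a drift of 3.321.

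N = 4 × (drift × SD / difference)² = 4 × (3.3211 × 24.08 / 9)² = 315.8, rounded up to 316, with power 0.900. The Table 5 stopping probabilities also reproduce. The arithmetic of Section 7.9 is right for its inputs.

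**2. Pooled SD implied by Section 7.16.** For shares p of grades A, B and C:

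- overall mean = Σ p × mean
- within-grade variance = Σ p × SD²
- between-grade variance = Σ p × (mean − overall mean)²
- pooled SD = √(within + between)

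Example, 60/20/20:

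- overall mean = 0.6 × 12.4 + 0.2 × 27.0 + 0.2 × 52.3 = 23.3
- within = 0.6 × 22.3² + 0.2 × 26.3² + 0.2 × 24.1² = 552.9
- between = 0.6 × 10.9² + 0.2 × 3.7² + 0.2 × 29.0² = 242.2
- pooled SD = √795.1 = 28.2

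**3. Power at N = 316 for 9 points, with the boundaries from step 1.** The mixes are assumptions, because the protocol gives none. The adjusted column uses the within-grade SD as the residual SD. It assumes the same 9-point effect in every grade.

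| A/B/C mix (%) | Pooled SD | Power, unadjusted | Within-grade SD | Power, grade-adjusted |
|---|---|---|---|---|
| 90/5/5 | 24.4 | 89.3% | 22.6 | 93.2% |
| 85/10/5 | 24.7 | 88.6% | 22.8 | 92.7% |
| 80/15/5 | 25.0 | 87.8% | 23.0 | 92.3% |
| 80/10/10 | 26.0 | 85.3% | 22.9 | 92.6% |
| 70/15/15 | 27.3 | 81.9% | 23.2 | 91.9% |
| 60/20/20 | 28.2 | 79.3% | 23.5 | 91.3% |
| 50/25/25 | 28.9 | 77.5% | 23.8 | 90.6% |
| Equal thirds | 29.4 | 76.1% | 24.3 | 89.5% |

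By SD alone, the unadjusted power is 90.0% at 24.08, 85.2% at 26, 82.6% at 27, 79.8% at 28 and 77.0% at 29.

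**4. Which mixes are compatible with 24.08?** On a 1% grid over all A/B/C mixes, the pooled SD is 24.08 or less in 75 of 5,151 cases. All of them have at least 77% grade A and at most 5% grade C. A sample made up only of grade C gives 24.10, just above.

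**5. Sample size for 90% with an unadjusted test.** The step 1 formula gives about 368 evaluable subjects at 80/10/10, 433 at 60/20/20 and 469 at equal thirds.

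**The case against.** A reader might infer that 24.08 is really a within-grade SD entered by mistake, since the root mean square of the three registry SDs is 24.3 and grade C alone has 24.1, and hence that the trial does not have 90% power. The documents do not support that. Section 7.9 describes 24.08 as coming from subjects of grades A, B and C combined, selected to match eligibility. On that description it is a pooled SD with the between-grade variance already inside it, and the sentence in Section 7.16 could be accurate. Numerical similarity is not evidence of an error.

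The registry figures are another data set, offered as an illustration, without the C4-C8 or 12-hour restriction and without the number of subjects per grade. The earlier cohort may have been nearly all grade A, or its grades may have differed less. The loss also depends on the mix: at 85/10/5 it is only between 1 and 2 points. All of this stands and limits the point to an unreconciled claim.

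Two further defences carry less weight. Section 7.12 foresees re-estimating the sample size if needed, which may recover power but does not support the 90% stated for 316 subjects. Section 7.9 adds 10%, to 351 enrolled, for loss to follow-up and possible adjustment for baseline factors, while the Synopsis assigns the same 10% to losses alone. Even 351 fully evaluable subjects fall short of the 368 needed at 80/10/10. Neither provision puts grade into the primary test. The SAP may do so, but the t-test, the SD, the 90% and the claim in Section 7.16 are stated in the protocol itself.

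**Conclusion.** The point holds as a failure to reconcile two sets of figures, not as a proven error. The calculation in Section 7.9 is correct for SD 24.08. The claim that variability by grade is covered agrees with the registry figures beside it only if the sample is at least about 77% grade A with almost no grade C, and the protocol states no mix. Under the assumed mixes, power for 9 points at 316 evaluable subjects runs from about 89% (90/5/5) through 85% (80/10/10) to 76% (equal thirds).

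This range rests on two assumptions: that the registry means and SDs apply to the trial population, and that the primary test stays unadjusted. The type I error and the validity of the test are not in question. What is missing is any demonstration that the 90% withstands a plausible grade mix, and adjustment for grade would make the answer matter far less.

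**What to change.** 1. In Section 7.6, replace the unadjusted t-test with a linear model of the change score on treatment and baseline impairment grade, keeping the one-sided alpha and the group-sequential boundaries. Grade is already recorded at screening. On the registry figures the residual SD is about 22.6 to 24.3 and power at 316 about 89.5% to 93%.

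2. In Sections 7.9 and 7.16, state the A/B/C mix of the cohort that gave 24.08, explain how that value fits with the registry figures, and qualify the statement that variability is fully covered. State that 90% holds at SD 24.08, and add the power of the unadjusted test at SD 26 to 29 (about 85% to 77%).

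3. Do not relabel 24.08 as a within-grade or residual SD unless the source data, which the sponsor holds, show that it is one.

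The cost is a protocol amendment, a look at data on file and a less favourable figure in print for the unadjusted test. No extra patients or assessments are needed if the adjusted analysis is adopted.
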